**Methods:**

This prospective, randomized controlled study is nested in a large-scale international project named “Enhancing therapy adherence among metastatic breast cancer patients” (Pfizer 65080791), aimed to develop a predictive model of nonadherence and associated DSS and guidelines to foster patients’ engagement and therapy adherence. A web-based DSS named TREAT (treatment adherence support) was developed using a patient-driven approach, with 4 sections, that is, Section A: Metastatic Breast Cancer; Section B: Adherence to Cancer Therapies; Section C: Promoting Adherence; and Section D: My Adherence Diary. Moreover, a machine learning–based web application was developed to predict patients' risk factors of adherence to anticancer treatment, specifically pertaining to physical status and comorbid conditions, as well as short and long-term side effects. Overall, 100 patients consecutively admitted at the European Institute of Oncology (IEO) at the Division of Medical Senology will be enrolled; 50 patients with metastatic breast cancer will be exposed to the DSS and machine learning web application for 3 months (experimental group), and 50 patients will not be exposed to the intervention (control group). Each participant will fill a weekly medication diary and a set of standardized self-reports evaluating psychological and quality of life variables (Adherence Attitude Inventory, Beck Depression Inventory-II, Brief Pain Inventory, 13-item Sense of Coherence scale, Brief Italian version of Cancer Behavior Inventory, European Organization for Research and Treatment of Cancer Quality of Life 23-item Breast Cancer-specific Questionnaire, European Organization for Research and Treatment of Cancer Quality of Life Questionnaire, 8-item Morisky Medication Adherence Scale, State-Trait Anxiety Inventory forms I and II, Big Five Inventory, and visual analogue scales evaluating risk perception). The 3 assessment time points are T0 (baseline), T1 (1 month), T2 (2 months), and T3 (3 months). This study was approved by the IEO ethics committee (R1786/22-IEO 1907).

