#### Participants

A sample of 100 patients enrolled consecutively in May 2023 in the IEO at the Division of Medical Senology with an MBC diagnosis. The enrollment started in May. Specifically, the observed outcomes of 50 patients with MBC exposed to the DSS (experimental group) and 50 patients with MBC not exposed to the intervention (control group) are evaluated.

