### Procedure

#### Randomization

Patients who signed the informed consent are given a unique identifier and assigned to either the control or intervention arm in a 1:1 ratio. First, the system asks to confirm all the inclusion and exclusion criteria. Then, an independent researcher generates a random sequence using the statistical language R (R Core Team 2020). Our randomization schedule involves an undisclosed blocking size that the data science team calculates without stratification. A patient is considered randomized when the randomization system assigns the patient an identification number according to a pre-established randomization list. We have created 2 different groups: the experimental group (n=50), in which each participant receives the link for the DSS and is trained to use the DSS for 3 months; and the control group (n=50), in which each patient receives standard care and suggestions bolstering adherence. Among all participants, the personal nonadherence risk is calculated through the preliminary version of the machine learning model to predict patients’ nonadherence behavior. 

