### Calculation of Sample Size

The sample size calculation was based on estimates for the effectiveness of TREAT as the primary outcome, assuming that the final analysis would be performed with a 2-sample 2-sided *t* test, a power of 96.4%, an α of .05, a standard deviation of 1.2, and a minimal difference in outcomes of 0.51 (effect size of 0.42) based on the patients’ self-reported satisfaction with the treatment decision [53]. Under these considerations, the final sample size was calculated to be 100 patients with MBC, with 50 individuals per group (50 patients with MBC exposed to DSS and 50 patients with MBC not exposed to the intervention). This sample size is expanded to 120 when a 20% attrition rate is used.

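### The enrolment target is 120 in the sample size section and 100 everywhere else, and 120 is not the right inflation for 20% attrition

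*Protocol article*

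**What the plan says.** In the protocol article, Calculation of Sample Size assumes a two-sample, two-sided t test with "a power of 96.4%, an α of .05, a standard deviation of 1.2, and a minimal difference in outcomes of 0.51 (effect size of 0.42"). It concludes that "the final sample size was calculated to be 100 patients with MBC, with 50 individuals per group", and closes with "This sample size is expanded to 120 when a 20% attrition rate is used".

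The other sections give these numbers:

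- **Abstract, Methods:** "Overall, 100 patients consecutively admitted at the European Institute of Oncology (IEO) at the Division of Medical Senology will be enrolled", split 50 and 50.
- **Participants:** "A sample of 100 patients enrolled consecutively in May 2023". The same paragraph then says that the outcomes of 50 exposed and 50 unexposed patients are evaluated.
- **Randomization:** patients are "assigned to either the control or intervention arm in a 1:1 ratio", and the groups formed are "the experimental group (n=50), in which each participant receives the link for the DSS" and a control group also of 50.
- **Primary End Point Analysis:** adherence is assessed in a sample of 100 patients at 3 months.

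Exploratory Analysis, under Statistical Considerations, plans imputation of missing values, followed by sensitivity analyses comparing results with and without it.

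**The concern.** A sample size section should yield two numbers: how many patients to randomise, and how many are expected to contribute an observed outcome. Here the section that allows for attrition gives 120, while the sections that describe enrolment and randomisation give 100 with no allowance. The primary end point section also uses 100, this time for the patients assessed at 3 months. If 20% of patients are lost, 100 cannot be the number enrolled, the number randomised and the number observed at 3 months all at once.

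Two things are at stake. A reader cannot tell whether recruitment is complete at 100 or at 120. And the precision of the 3-month comparison depends on the answer: under the plan's own attrition rate the two targets leave different numbers observed, and neither leaves 100.

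**Working it through.** **Inputs**

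- From Calculation of Sample Size: 100 patients required (50 per group); attrition 20%; inflated total 120; difference 0.51; SD 1.2; two-sided α 0.05.
- From Randomization: allocation 1:1.

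**1. Reproducing the 120**

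100 × (1 + 0.20) = 120, which matches. The plan therefore added 20% of the required number.

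**2. The inflation that 20% attrition calls for**

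Attrition is a share of those enrolled, so the target N must satisfy N × (1 − 0.20) = 100.

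- N = 100 / 0.80 = 125.
- Per arm: 50 / 0.80 = 62.5, rounded up to 63, so 126 in total with equal arms.
- Loss that 120 can absorb: 1 − 100/120 = 16.7%.

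**3. Patients left at 20% loss**

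| Randomised | Observed at 3 months | Per arm |
|---|---|---|
| 120 (Calculation of Sample Size) | 120 × 0.80 = 96 | 48 |
| 100 (Abstract, Randomization) | 100 × 0.80 = 80 | 40 |
| 126 (corrected, equal arms) | 126 × 0.80 = 100.8 | about 50 |

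**4. Effect on power and precision**

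These are complete-case figures: only patients with an observed outcome count. The standardised difference is d = 0.51 / 1.2 = 0.425, which the plan rounds to 0.42. Power comes from the noncentral t distribution with 2n − 2 degrees of freedom and noncentrality d × √(n/2).

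| n per arm | Noncentrality | Critical t | Power |
|---|---|---|---|
| 50 | 0.425 × √25 = 2.125 | 1.984 | 55.7% |
| 48 | 0.425 × √24 = 2.082 | 1.986 | 54.0% |
| 40 | 0.425 × √20 = 1.901 | 1.991 | 46.7% |

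The inflation slip (50 to 48 per arm) costs 55.7 − 54.0 = 1.7 percentage points. Using no inflation (50 to 40 per arm) costs 55.7 − 46.7 = 9.0 points.

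The difference detectable with 80% power is 0.57 SD at 50 per arm and 0.63 SD at 40. With the plan's SD of 1.2, that is 0.57 × 1.2 = 0.68 and 0.63 × 1.2 = 0.76 units, against the planned 0.51.

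**5. Keeping this apart from the stated power**

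The first row of the table has no attrition at all, and it already gives 55.7% rather than the stated 96.4%. Reaching 96.4% at d = 0.425 would take about 158 per arm. That discrepancy lies in the basic calculation.

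**The case against.** **The arithmetic slip is small.** Multiplying by 1.2 instead of dividing by 0.8 loses four patients and under 2 points of power, and 120 would do if attrition stayed at or below 16.7%. This stands. The miscalculation alone would be a minor correction, so the conflict between 100 and 120 has to carry the point.

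**100 can be read as the evaluated number.** Primary End Point Analysis and the last sentence of Participants support this: 120 would be enrolled and 100 evaluated. But the Abstract attaches 100 to enrolment and Randomization attaches 50 to each randomised group. Even on this reading, 120 at 20% loss gives 96. The ambiguity is real and the text does not resolve it.

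**Imputation keeps everyone in the analysis.** A reader might infer that the number analysed must fall short whichever target applies. The document does not support that. It assumes that the full 20% is lost and that those patients are dropped, whereas Exploratory Analysis plans imputation, so all randomised patients could be analysed. What remains is that imputation does not generally restore the information in outcomes never observed, and that the planned analyses without imputation would rest on the smaller number. The figures for 48 and 40 per arm must therefore be labelled complete-case at 20% loss.

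**The low power is not an attrition effect.** A reader might also set 46.7% against 96.4% and blame the missing allowance. Most of that gap, 96.4 − 55.7 = 40.7 points, is present with no attrition. Attrition accounts for at most the further 9.0.

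**Conclusion.** The point holds as an inconsistency in the stated enrolment target, together with a minor miscalculation. The document gives both 100 and 120 without saying which is to be randomised. It uses 100 for patients enrolled, randomised and assessed at 3 months, which leaves no attrition allowance outside the one sentence that introduces it. The 120 is itself five short of 125, or six short of 126 with equal arms.

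At the plan's own 20% loss, the expected number with observed outcomes is about 96 if 120 are randomised and about 80 if 100 are. On a complete-case two-sided t test at d = 0.425, the cost relative to 50 per arm is 1.7 or 9.0 points of power respectively. These sizes rest on the stated attrition being fully realised and spread evenly between arms, and on missing outcomes adding no information.

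The contradiction should be corrected because it is verifiable and cheap to remove. Correcting it would not make the sample adequate for the stated 96.4% power, which is a separate error.

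**What to change.** State one randomised target and one expected number with observed 3-month outcomes. Use both consistently in the Abstract, Primary End Point Analysis, Participants, Randomization and Calculation of Sample Size. Depending on the target:

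- **If 100 is kept:** say that about 80 patients (40 per arm) would have observed outcomes at 20% loss, and restate power and the detectable difference for 40 per arm.
- **If 120 is kept:** say that it leaves about 96 (48 per arm), change the 100 and 50 + 50 in the enrolment and randomisation text to 120 and 60 + 60, and restate power for 48 per arm.
- **If 100 observed outcomes are required at 20% loss:** replace 120 with 126 (63 per arm).

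In each case, label the restated figures as complete-case, and note that the planned imputation keeps patients in the analysis without generally recovering the lost information. Correct the 96.4% power statement as a separate item.

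The first option costs only wording, but it means stating openly that power at the planned difference is about 47%. The second needs 20 more patients, and the third 26 more, than the 100 in the enrolment and randomisation text. Restating the numbers is enough to resolve this point; enrolling more is not required for it.

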### Statistical Considerations

#### Exploratory Analysis

Our exploratory analysis will start with a visual exploration of all variables to evaluate the frequency, percentage, and near-zero variance for categorical variables (eg, gender, cancer stage); distribution for numeric variables (eg, age); and their corresponding missing value patterns [54]. Near-zero variance is found when a categorical variable has a small percentage of a given category and will be addressed by recategorization. We will consider variable transformations such as logarithmic, Box-Cox, or categorization of numeric variables that do not present a normal distribution. Missing values will be handled through imputation algorithms followed by sensitivity analyses to verify whether our results are stable with and without imputation [53]. Comparisons for the exploratory analysis will be conducted through analysis of variance (2-sided *t* tests being a category of analysis of variance) and chi-square tests (Fisher exact test when any cell presented a frequency below 5).

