## Methods

### Primary End Point Analysis

The primary end point was to assess the effectiveness of the DSS web-based solution and the machine learning web application in promoting adherence to OATs in a sample of 100 patients with MBC at 3 months. The adherence is evaluated using the number of pills taken divided by the number of pills prescribed. Further, the adherence is assessed using behavioral measures: the 8-item Morisky Medication Adherence Scale (MMAS-8) [31] and Adherence Attitude Inventory (AAI) [32].

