#### Adherence Medication Diary

A weekly paper diary is given to patients to monitor their medication intake. The diary will assess if medications are taken as prescribed and the possible reasons for not taking pills (eg, side effects, forgetfulness, no pill refill). The data collected refer to the number of pills not taken per week and the number of pills established according to the patient medical prescription protocol per week as well as planned interruptions. Further, the diary evaluates and monitors the side effects, their intensity (from 0 to 10) associated with the therapy intake, and their emotions, thoughts, behaviors, and consequences.

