### Timeline

There are 3 assessment time points. At the baseline (T0), all patients fill a set of validated measures (MMAS-8, AAI, STAI-Y forms I and II, BDI-II, CBI-B/I, SOC-13, BPI, EORTC-QLQ-C30, EORTC-QLQ-BR23, BFI, and visual analogue scale). The expected time to complete all the given questionnaires at baseline is approximately 40 minutes. Access to DSS is given to the experimental group for 3 months. At T1 and T2, the following questionnaires are filled: MMAS-8, AAI, STAI-Y form I, BDI-II, CBI-B/I, EORTC-QLQ-C30, and EORTC-QLQ-BR23. Further, all patients have to fill a weekly adherence medication diary for 3 months. Variables that are not sensitive to change, for example, personality (BFI) and anxiety traits (STAI-Y form II) are collected only at T0. Each month, all participants receive a brief telephone interview in which they are monitored for adherence to the research protocol. Two psychologists perform the monthly telephone interview to monitor the filling out of the questionnaires and the medication adherence diary supporting patients with MBC in this task, barriers, and concerns related to the study participation. At T3 (3 months), all behavioral and psychological measures are filled, and an interview (online or vis-à-vis) is performed.

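### Stable results with and without imputation could be falsely reassuring for the diary-based pill ratio, because that check cannot detect diary return that depends on unrecorded adherence

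*Protocol article*

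**What the plan says.** Primary End Point Analysis defines the outcome: "The adherence is evaluated using the number of pills taken divided by the number of pills prescribed". MMAS-8 and AAI are further adherence measures.

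The pill data come from the patient. Adherence Medication Diary states: "A weekly paper diary is given to patients to monitor their medication intake", and "The data collected refer to the number of pills not taken per week". The weekly prescribed number and planned interruptions are recorded there as well. An unreturned diary is therefore a missing week of the pill ratio.

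Exploratory Analysis gives the handling of missing data: "Missing values will be handled through imputation algorithms followed by sensitivity analyses to verify whether our results are stable with and without imputation". The imputation algorithm and its assumption are not named. The same section also plans a descriptive look at the variables "and their corresponding missing value patterns". The weighting under Propensity Score balances baseline covariates between arms and does not address diary return.

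Two other statements bear on the point. Calculation of Sample Size says "This sample size is expanded to 120 when a 20% attrition rate is used". Timeline says "Two psychologists perform the monthly telephone interview to monitor the filling out of the questionnaires and the medication adherence diary".

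**The concern.** The article names a specific test of robustness: whether results agree with and without imputation. Both sides of that comparison rely on the returned diaries. A complete-case analysis takes the missing weeks to resemble the returned ones. The usual imputation does the same after conditioning on observed data. Neither lets return depend on the adherence that was not recorded.

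For this outcome that dependence is plausible, because stopping the pills and stopping the record of them can have the same cause. Experimental patients are trained on a website that has its own diary section, and controls receive standard care. Patients therefore know their arm, and return could differ between arms. Limitations of This Trial acknowledges questionnaire burden, recall bias and overestimated adherence, but not diaries missing because pills were skipped.

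At stake is a pill-ratio comparison reported as robust because two analyses agree, when both are off in the same direction.

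**Working it through.** **Figures in the plan.** No stated figure measures this risk. The nearest is the attrition allowance, 100 × 1.2 = 120. It is borrowed below only as a convenient missing fraction of 20%; it is patient attrition, not weekly diary non-return.

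**Step 1: do the two analyses separate when return depends on adherence?** Assumptions not in the documents: adherence normal with SD 15 percentage points; control mean 85; true effect 0 or 5; log-odds of missing = ln(m/(1−m)) − s × (y − 85)/15. Where return depends on adherence, s = 1 and m = 0.165; where missing is random, s = 0 and m = 0.20. Each gives about 20% missing (16% in the experimental arm when the dependent rule meets a 5-point effect). Imputation is by regression within arm on one auxiliary variable, assuming missing at random. Large-sample results (2,000,000 per arm), experimental minus control, in points:

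| Missing depends on adherence in | True | Complete-case | Imputed, auxiliary r = 0.1 | r = 0.4 | r = 0.8 |
|---|---|---|---|---|---|
| Experimental arm only | 0 | 2.64 to 2.65 | 2.62 | 2.26 | 1.03 |
| Control arm only | 5 | 2.31 to 2.36 | 2.33 | 2.74 | 3.94 |
| Both arms, same rule | 5 | 4.46 to 4.50 | 4.46 | 4.56 | 4.81 |

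A trial-sized simulation (60 per arm, 2000 runs, 10 imputations, r = 0.4) covers the same rule in both arms with no true effect. The experimental arm's mean is too high by 2.66 (complete-case) and 2.29 (imputed), but the between-arm difference is 0.06 in both, so it is essentially unbiased.

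**Step 2: would the check raise a flag?** In the first row at r = 0.4 the analyses differ by 2.64 − 2.26 = 0.38 points, and both are more than 2 points from the truth. Under the same SD, the standard error of the effect with 50 per arm is 15 × √(2/50) = 3.0. A gap of 0.38 would be read as stable. At r = 0.8 the gap is 2.65 − 1.03 = 1.62, which might be noticed.

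**Step 3: what would a delta adjustment show?** If a fraction f of an arm is missing and its imputed adherence is lowered by δ, that arm's mean falls by f × δ. The effect changes by −(f_E × δ_E − f_C × δ_C). With f = 0.20 and the shift in one arm only:

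- δ = 5: 0.20 × 5 = 1.0 point
- δ = 10: 0.20 × 10 = 2.0 points
- δ = 20: 0.20 × 20 = 4.0 points

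Equal f and equal δ in both arms cancel, which is why the shift must be set separately by arm.

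**Step 4: is scoring unreturned weeks as not taken a safe alternative?** Assume 75% and 85% return in the two arms and adherence of 0.85 among returned weeks in both. The scored ratios are 0.75 × 0.85 = 0.6375 and 0.85 × 0.85 = 0.7225. The rule alone creates a difference of 0.085, or 8.5 points, in favour of the arm that returns more diaries. It is not conservative for a between-arm comparison.

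**The case against.** Reporting results with and without imputation is ordinary practice. The sentence is generic, sits under Exploratory Analysis and covers all variables. A condensed article may leave further sensitivity analyses to a fuller plan. That stands as far as the absence of detail goes: silence here does not show that no other analysis is planned. But the article does state a criterion for stability, and that criterion cannot address outcome-dependent diary return.

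The planned check is not powerless. Useful auxiliaries are collected: each patient's other diary weeks, and MMAS-8 and AAI from T0 to T3. If they predict pill-taking strongly, imputation removes part of the bias and the two analyses move apart. Their correlation with pill-taking is not given, so neither the weak nor the strong case can be assumed.

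The monthly calls support diary completion, and MMAS-8 and AAI measure adherence without the diary. Both reduce the risk without removing it.

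A reader might infer that the two analyses share an identical bias. The table shows a shared direction, not a shared size. A reader might also take the 20% in the sample-size section as the expected diary loss. It is patient attrition, and the progression and declining function named under Limitations of This Trial need not reflect skipped pills.

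**Conclusion.** The point holds in a limited form. The stated check could be falsely reassuring for the pill ratio, because complete-case analysis and missing-at-random imputation tend to be biased in the same direction when return depends on unrecorded adherence. The treatment effect is distorted when that dependence, or the adherence distribution, differs by arm.

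The documents do not support saying that the comparison will be biased, or by how much. With one rule in both arms and no true effect, only the arm means are inflated. With a true effect of 5 points and one rule in both arms, the estimate falls only to about 4.5 in the complete-case analysis. The larger distortions need missingness that depends on adherence in one arm only, which is an assumption. Any figure for an inflated false-positive rate would rest on the same kind of assumption.

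The conclusion also assumes that the unnamed algorithm is of the usual missing-at-random kind and that the analysis without imputation uses complete cases. The shifts of 1, 2 and 4 points are illustrations. This is a cheap improvement.

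**What to change.** Keep both planned analyses and, for the pill ratio:

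1. Include the other diary weeks, MMAS-8 and AAI as auxiliary variables in the imputation.
2. Report diary return by arm.
3. Add a delta-adjusted tipping-point analysis that shifts imputed adherence downward separately in each arm. Judge robustness on whether the delta that overturns the conclusion is plausible, not on agreement with and without imputation.

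Do not use unreturned weeks scored as not taken as a robustness criterion. At most, report it as an extreme scenario, with prescribed pills and planned interruptions taken from records; otherwise the denominator for those weeks may be unknown and planned interruptions could be scored as nonadherence.

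The cost is a paragraph of analysis wording, a few extra model runs, and a conclusion that may have to be stated less firmly. The extreme scenario, if reported, also needs prescription records for the unreturned weeks.
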